## Visit 1: TAMPA SCALE for KINESIOPHOBIA

To be completed by study coordinator

**Directions:** Please read each of the following statements and circle the number that best represents your feelings.

|                                                                                                                                   | Strongly Disagree | Disagree | Agree | Strongly Agree |
|-----------------------------------------------------------------------------------------------------------------------------------|-------------------|----------|-------|----------------|
| I'm afraid that I might injure myself if I exercise.                                                                              | 1                 | 2        | 3     | 4              |
| If I were to try to overcome it, my pain would increase.                                                                          | 1                 | 2        | 3     | 4              |
| My body is telling me I have something dangerously wrong.                                                                         | 1                 | 2        | 3     | 4              |
| My pain would probably be relieved if I were to exercise.                                                                         | 1                 | 2        | 3     | 4              |
| People aren't taking my medical condition seriously enough.                                                                       | 1                 | 2        | 3     | 4              |
| My accident has put my body at risk for the rest of my life.                                                                      | 1                 | 2        | 3     | 4              |
| Pain always means I have injured my body.                                                                                         | 1                 | 2        | 3     | 4              |
| Just because something aggravates my pain does not mean it is dangerous.                                                          | 1                 | 2        | 3     | 4              |
| I am afraid that I might injure myself accidentally.                                                                              | 1                 | 2        | 3     | 4              |
| Simply being careful that I do not make any unnecessary movements is the safest thing I can do to prevent my pain from worsening. | 1                 | 2        | 3     | 4              |
| I wouldn't have this much pain if there weren't something potentially dangerous going on in my body.                              | 1                 | 2        | 3     | 4              |
| Although my condition is painful, I would be better off if I were physically active.                                              | 1                 | 2        | 3     | 4              |
| Pain lets me know when to stop exercising so that I don't injure myself.                                                          | 1                 | 2        | 3     | 4              |
| It's really not safe for a person with a condition like mine to be physically active.                                             | 1                 | 2        | 3     | 4              |
| I can't do all the things normal people do because it's too easy for me to get injured.                                           | 1                 | 2        | 3     | 4              |
| Even though something is causing me a lot of pain, I don't think it's actually dangerous.                                         | 1                 | 2        | 3     | 4              |
| No one should have to exercise when he/she is in pain.                                                                            | 1                 | 2        | 3     | 4              |

Score: \_\_\_\_\_

**Investigator Signature:** \_\_\_\_\_

**Date:** \_\_\_\_\_

DAY-MONTH-YEAR

Participant ID # \_\_\_\_\_

Visit Date \_\_\_\_/\_\_\_\_/\_\_\_\_

## Visit 1: SCREENING CHECKLIST – INCLUSION/EXCLUSION CRITERIA

To be completed by study coordinator

|                                                                                                                                                                                                                                                                                                                                            | Yes | No |
|--------------------------------------------------------------------------------------------------------------------------------------------------------------------------------------------------------------------------------------------------------------------------------------------------------------------------------------------|-----|----|
| 18-45 years of age                                                                                                                                                                                                                                                                                                                         |     |    |
| Answers yes to the following question: "Have you had low back pain constantly or on most days for the last three months?"                                                                                                                                                                                                                  |     |    |
| Answer yes to the following question: "Has your back pain caused you to seek care or consultation from a health care provider?"                                                                                                                                                                                                            |     |    |
| Pain intensity rating over the past week $\geq 2$ on a 0-10 numerical pain scale                                                                                                                                                                                                                                                           |     |    |
| RMDQ score $\geq 4$                                                                                                                                                                                                                                                                                                                        |     |    |
| Exhibit 3 of 4 of the following findings reported in the clinical prediction rules for spinal manipulation                                                                                                                                                                                                                                 |     |    |
|  FABQ work subscale score < 19                                                                                                                                                                                                                                                                                     |     |    |
|  No symptoms distal to the knee                                                                                                                                                                                                                                                                                    |     |    |
|  At least 1 hypo-mobile lumbar spinal segment                                                                                                                                                                                                                                                                      |     |    |
|  At least 1 hip > 35 degrees internal rotation range of motion                                                                                                                                                                                                                                                     |     |    |
| No personal history of excluded disorders – Alzheimer's, amyotrophic lateral sclerosis, multiple sclerosis, Parkinson's, stroke, congestive heart failure, heart attack in the past 24 months, rheumatoid arthritis, spine or pathologic fractures, avascular necrosis, osteonecrosis, severe osteoarthritis, blindness, or active cancer. |     |    |
| No history of spine surgery or hip arthroplasty                                                                                                                                                                                                                                                                                            |     |    |
| No use of narcotics or muscle relaxants within 30 days prior to study entry                                                                                                                                                                                                                                                                |     |    |
| Not pregnant, lactating, or anticipate becoming pregnant in the next 3-months                                                                                                                                                                                                                                                              |     |    |
| No BMI > 35 kg/m                                                                                                                                                                                                                                                                                                               |     |    |
| No clinical depression – CESD score $\geq 24$                                                                                                                                                                                                                                                                                              |     |    |
| No unexplained weight loss > 10lbs over the past month                                                                                                                                                                                                                                                                                     |     |    |
| No pending litigation related to LBP                                                                                                                                                                                                                                                                                                       |     |    |
| No disability services related to LBP                                                                                                                                                                                                                                                                                                      |     |    |
| No manual therapy treatment of the spine 30 days prior to first study intervention                                                                                                                                                                                                                                                         |     |    |
| No drug or alcohol use that would interfere with adherence to study requirements                                                                                                                                                                                                                                                           |     |    |

Did the participant meet the eligibility requirements for this study?

- ☐ Yes (If yes, continue to next form)  
☐ No (If no, complete "Study Completion Form")

Investigator Signature: \_\_\_\_\_

Date: \_\_\_\_\_

DAY-MONTH-YEAR

Participant ID # \_\_\_\_\_

Visit Date \_\_\_\_/\_\_\_\_/\_\_\_\_

## Visit 1: SCREENING CHECKLIST - LIMITING CRITERIA

*To be completed by study coordinator*

| The following questions exclude the participant from certain experiments, but do not exclude the participant from enrolling as a study participant:                                                             | YES | NO |
|------------------------------------------------------------------------------------------------------------------------------------------------------------------------------------------------------------------------|-----|----|
| Have a personal or family history of epilepsy or seizures, migraine headaches within 6-months (186 days) of V2 physiologic testing, or taking medications in the benzodiazepine class (Exclude from Experiment 3 TMS). |     |    |
| Have contraindications for exposure to a magnetic field (Exclude from Experiment 1 MRI and Experiment 3 TMS).                                                                                                          |     |    |
| Have any other contraindications for participating in any of the 3 study experiments. Explain:                                                                                                                         |     |    |

Does the candidate have any conditions qualifying for exclusion from experiments for this study?

☐ Yes (If yes, complete "Experiment Exclusion Section" of "Randomization and Enrollment Form")

☐ No

**Investigator Signature:** \_\_\_\_\_

**Date:** \_\_\_\_\_

DAY-MONTH-YEAR

Participant ID # \_\_\_\_\_

Visit Date \_\_\_\_/\_\_\_\_/\_\_\_\_

## Visit 1: ENROLLMENT AND RANDOMIZATION

*To be completed by study coordinator*

Is the participant eligible for the study based on inclusion and exclusion criteria?

- ☐ Yes (If yes, date enrolled \_\_\_\_\_ and randomized if different \_\_\_\_\_)  
Day-Month-Year Day-Month-Year
- ☐ No (If no, leave the rest of the form blank.)

If eligible and not randomized, indicate reason:

- ☐ Failed to return ☐ Declined participation
- ☐ Other (specify): \_\_\_\_\_

**Experiment Exclusion Section:** The candidate is **excluded** from participating in the following experiment(s):

- ☐ Experiment 1 (Muscular): MRI
- ☐ Experiment 2 (Spinal): Biomechanics
- ☐ Experiment 3 (Cortical): TMS

Participant is available\* for the following experiments:

- ☐ 1 Muscular - MRI
- ☐ 2 Spinal - Biomechanics
- ☐ 3 Cortical - TMS

\*Participant being "available" is based on: 1) meeting inclusion/exclusion criteria for a given experiment; 2) the experimental protocol being open to enrollment; and 3) the study participant and laboratory schedules align.

Participant assigned to Experiment:

- ☐ 1 Muscular - MRI
- ☐ 2 Spinal - Biomechanics
- ☐ 3 Cortical - TMS

Participant randomly assigned to Intervention Arm:

- ☐ 1 Manipulation
- ☐ 2 Mobilization
- ☐ 3 Laser

**Parking passes needed?**

- ☐ Yes
- ☐ No

**Investigator Signature:** \_\_\_\_\_

**Date:** \_\_\_\_\_

DAY-MONTH-YEAR

Participant ID # \_\_\_\_\_

Visit Date \_\_\_\_/\_\_\_\_/\_\_\_\_

## VISIT 1: SCREENING CHECKLIST

*To be completed by study coordinator*

Did the participant attend this visit? ☐ Yes (if yes, continue) ☐ No

Please check all assessments completed at this visit:

Visit Name: Screening

- |                                                   |                                                                  |
|---------------------------------------------------|------------------------------------------------------------------|
|  Informed Consent         |  Medication History                      |
|  Medical History – Part 1 |  Physical Exam 1                         |
|  NPR                      |  Physical Exam 2                         |
|  RMDQ                     |  TSK                                     |
|  CES-D                    |  Medical History – MRI Contraindications |
|  FABQ                     |  Criteria Checklists (3)                 |
|  Medical History – Part 2 |  Enrollment & Randomization              |

Is the participant continuing in the study?

- ☐ Yes (if yes, complete a RANDOMIZATION AND ENROLLMENT form)  
☐ No (if no, complete a STUDY COMPLETION form)

Comments:

\_\_\_\_\_

Investigator Signature: \_\_\_\_\_

Date: \_\_\_\_\_

DAY-MONTH-YEAR

# Visit 2

Investigator Signature:

Date:

DAY-MONTH-YEAR

Participant ID # \_\_\_\_\_

Visit Date \_\_\_\_/\_\_\_\_/\_\_\_\_

## Visit 2: PRIOR AND CONCOMITANT MEDICATIONS

*To be completed by study coordinator*

Have you taken any medications (including over the counter pain relief medications) or used heat or ice for your back pain in the past 7 days?

☐ No ☐ Yes (If YES, record below.)

| Medication/Modality | Frequency and Dose | Indication | Start Date | Stop Date | Ongoing                  |
|---------------------|--------------------|------------|------------|-----------|--------------------------|
| 1.                  |                    |            |            |           |  |
| 2.                  |                    |            |            |           |  |
| 3.                  |                    |            |            |           |  |
| 4.                  |                    |            |            |           |  |
| 5.                  |                    |            |            |           |  |

Investigator Signature: \_\_\_\_\_

Date: \_\_\_\_\_

DAY-MONTH-YEAR

Participant ID # \_\_\_\_\_

Visit Date \_\_\_\_/\_\_\_\_/\_\_\_\_

## Visit 2: CHANGE IN MEDICATION USE

*To be completed by study coordinator*

Have you had any changes in medication use NOT related to your back pain in the past 7 days?

☐ No ☐ Yes (If YES, record below.)

| Medication | Indication* | Dose & Frequency | Start Date | Stop Date | Ongoing                  |
|------------|-------------|------------------|------------|-----------|--------------------------|
| 1.         |             |                  |            |           |  |
| 2.         |             |                  |            |           |  |
| 3.         |             |                  |            |           |  |
| 4.         |             |                  |            |           |  |
| 5.         |             |                  |            |           |  |

\*If Indication is related to a negative change in health status, alert study coordinator, complete Health Status Reassessment and enter in Adverse Event Log.

Notes:

Investigator Signature: \_\_\_\_\_

Date: \_\_\_\_\_

DAY-MONTH-YEAR

Participant ID # \_\_\_\_\_

Visit Date \_\_\_\_/\_\_\_\_/\_\_\_\_

## Visit 2: HEALTH STATUS REASSESSMENT

*To be completed by study staff*

Since your last visit, have you had any change in your health?

☐ No ☐ Yes (If YES, record below, alert study coordinator, and complete Adverse Event log.)

|                                                                                                                                            |                                                                  |
|--------------------------------------------------------------------------------------------------------------------------------------------|------------------------------------------------------------------|
| Change & Symptoms                                                                                                               |                                                                  |
| Describe:

Start Date:
Stop Date:
Missed work or school? _____ days | Treatment:

Outcome: |
| Change & Symptoms                                                                                                               |                                                                  |
| Describe:

Start Date:
Stop Date:
Missed work or school? _____ days | Treatment:

Outcome: |
| Change & Symptoms                                                                                                               |                                                                  |
| Describe:

Start Date:
Stop Date:
Missed work or school? _____ days | Treatment:

Outcome: |

**Investigator Signature:** \_\_\_\_\_

**Date:** \_\_\_\_\_

DAY-MONTH-YEAR

Participant ID # \_\_\_\_\_

Visit Date \_\_\_\_/\_\_\_\_/\_\_\_\_

## Visit 2: CONTRAINDICATIONS FOR INTERVENTION

*To be completed by study staff*

**Have you had any of the  
following symptoms?\***

**If YES, describe here:**

|                                                                      |                                                                 |  |
|----------------------------------------------------------------------|-----------------------------------------------------------------|--|
| Radiating pain
(burning,
numbness, or
tingling in the legs) |  Yes

 No |  |
| Muscle weakness
in the legs                                       |  Yes

 No |  |
| Episodes of
incontinence of
bowel or bladder                   |  Yes

 No |  |

\*If YES, describe in right column, refer to clinician for Health Status Reassessment Physical Exam, and complete Adverse Event Log (forms located in Appendix).

**Investigator Signature:** \_\_\_\_\_

**Date:** \_\_\_\_\_

DAY-MONTH-YEAR

Participant ID # \_\_\_\_\_

Visit Date \_\_\_\_/\_\_\_\_/\_\_\_\_

## Visit 2: CONTRAINDICATIONS FOR LAB TESTING

To be completed by study staff

| Lab Testing Group        |                   | Since your last visit have you had any of the following?                                                     |                                                             | If yes, describe and consult PI                                                                                                                                                                                                                                                                                                                                    |
|--------------------------|-------------------|--------------------------------------------------------------------------------------------------------------|-------------------------------------------------------------|--------------------------------------------------------------------------------------------------------------------------------------------------------------------------------------------------------------------------------------------------------------------------------------------------------------------------------------------------------------------|
|  | 1
Muscular MRI | Contraindications for exposure to a magnetic field?
(Must complete Magnetic Field Contraindications form) |  Yes
 No |                                                                                                                                                                                                                                                                                                                                                                    |
|  | 2
Spinal MCL   | Muscle weakness in the legs?                                                                                 |  Yes
 No |                                                                                                                                                                                                                                                                                                                                                                    |
|                          |                   | Episodes of incontinence of bowel or bladder?                                                                |  Yes
 No |                                                                                                                                                                                                                                                                                                                                                                    |
|                          |                   | New or previously unreported muscle, bone or joint injury?                                                   |  Yes
 No | Date: _____                                                                                                                                                                                                                                                                                                                                                        |
|  | 3
Cortical TMS | Contraindications for exposure to a magnetic field?                                                          |  Yes
 No |                                                                                                                                                                                                                                                                                                                                                                    |
|                          |                   | Migraine headache 6-months prior to V2 physiologic assessments?                                              |  Yes
 No | Administer ID Migraine Screener:
Sensitivity to light?  Yes  No
Nausea or vomiting?  Yes  No
Disabling intensity?  Yes  No
*if at least 2 symptoms, cancel TMS testing
Date of last migraine: _____ |
|                          |                   | Taking medications in the benzodiazepine class?                                                              |  Yes
 No |                                                                                                                                                                                                                                                                                                                                                                    |
|                          |                   | Recent concussion?                                                                                           |  Yes
 No |                                                                                                                                                                                                                                                                                                                                                                    |

If YES, describe in right column, refer to PIs, and complete Adverse Event Log (forms located in Appendix).

Investigator Signature: \_\_\_\_\_

Date: \_\_\_\_\_

DAY-MONTH-YEAR

Participant ID # \_\_\_\_\_

Visit Date \_\_\_\_/\_\_\_\_/\_\_\_\_

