### 4.2 Exclusion Criteria

To be eligible for the study participants must not:

- Have a personal history of the following neurological disorders: Alzheimer’s, Amyotrophic Lateral Sclerosis, Multiple Sclerosis, Parkinson’s, Stroke
- Have a personal history of the following cardiorespiratory disorders: Congestive heart failure, Heart attack in past 24 months
- Have a personal history of the following musculoskeletal disorders: Rheumatoid Arthritis, pathologic fractures of the spine, avascular necrosis or osteonecrosis, severe osteoarthritis. Including a history of spine surgery or a hip arthroplasty
- Have active cancer
- Be Blind
- Have used narcotics or muscle relaxants within 30 days prior to study enrollment.
- Report being pregnant, lactating, or that they anticipate becoming pregnant in the next 3-months
- Have a body mass index greater than 35 kg/m^2
- Have clinical depression (i.e., subjects who score 24 or higher on the Center for Epidemiology Depression Scale).
- Report unexplained weight loss over the past month ( $>10$  lbs).

- Report they have pending litigation related to an episode of LBP or are receiving any type of disability services related to low back pain.
- Report having received any manual therapy intervention applied to the spine 30 days prior to first study intervention.
- Current drug or alcohol use or dependence that, in the opinion of the PIs, would interfere with adherence to study requirements.
- Applies to Experiment 3 (Cortical Effects) only: Have a personal or family history of epilepsy or seizures, Migraine Headaches within 6 months (186 days) of V2 physiologic testing, or taking medications in the benzodiazepine class.
- Applies to Experiments 1 and 3 (Muscular Effects and Cortical Effects) only: Have contraindications for exposure to a magnetic field.
- Applies to Experiment 1 (Muscular Effects) only: Have a positive result from pregnancy test administered the day of each MRI.

The supplemental research will enroll an additional 60 healthy participants with no history of LBP and who are matched on sex, age ( $\pm 3$  years), height ( $\pm 2$  inches), and weight ( $\pm 10$  lbs) to the participants recruited into **Experiment 2** of the RELIEF study. The same exclusion criteria are applied to the control group as is used for the RELIEF study LBP participants.

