### 7.1 Specification of Safety Parameters

At visits 2-9 the study staff will use the Health Status Reassessment CRF to ask the study participants if they have had any change in general health since the last visit. If fever or unexplained weight loss is reported, suggesting systemic infection / disease may be causing their low back pain, the clinician will do a basic physical exam and specifically assess for the possibility they have other systemic illness. They will be advised to seek medical care and research participation may be delayed, temporarily discontinued, or permanently suspended at the discretion of the examining clinician and in consultation with the Medical Directors if needed.

Before each treatment the study staff will use the Contraindications for Intervention CRF to inquire about change in back related signs indicative of increased severity of symptoms. Specifically if they have any increases in 1) radiating pain (i.e., burning, numbness, tingling sensations into the legs), 2) have noticed any muscle weakness in the legs, and 3) have any episodes of incontinence of bowel or bladder. If the study participant reports yes on any of these items the clinician will do a basic physical exam and assess neurological function by checking

myotomes, dermatomes, and reflexes to determine whether the study participant now presents with hard neurological signs (e.g., loss of motor function, significant changes in reflexes), or symptoms of other systemic disease. If the participant does present with hard neurological signs or serious systemic disease, they will be encouraged to seek consultation with their personal physician, and they will be excluded from further participation from the study.

Before each experimental measurement lab testing session (Visits 2, 8, and 9) the study staff will use the Contraindications for Lab Testing CRF to inquire specifically about symptoms of health issues contraindicated for the allocated experimental measurement lab test. Migraine headache will be assessed using The ID Migraine™ self-administered screener. If a possible contraindication is identified the PIs are consulted to determine safety before the lab testing begins.

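### The pre-test form for TMS at Visits 2, 8 and 9 re-asks every Experiment 3 exclusion in Section 4.2 except seizure history, leaving new seizures to indirect reporting

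*Supplement*

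**What the plan says.** Section 4.2 of the protocol (v6.0) has an exclusion that begins "Applies to Experiment 3 (Cortical Effects) only: Have a personal or family history of epilepsy or seizures" and goes on to recent migraine and benzodiazepines. A separate 4.2 item, shared with Experiment 1, excludes people with contraindications to a magnetic field. The Visit 1 limiting-criteria checklist repeats all of these.

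Section 7.1 describes the later check: "Before each experimental measurement lab testing session (Visits 2, 8, and 9) the study staff will use the Contraindications for Lab Testing CRF". Its purpose is "to inquire specifically about symptoms of health issues contraindicated for the allocated experimental measurement lab test". If a possible contraindication is found, the PIs are consulted before testing starts.

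The Cortical TMS block of that form (CRFs v5.0, April 2016) has four rows at Visit 2: "Contraindications for exposure to a magnetic field", "Migraine headache 6-months prior to V2 physiologic assessments", "Taking medications in the benzodiazepine class" and "Recent concussion". The Visit 8 and Visit 9 forms carry the same four rows. The question stem covers the time since the last visit, and a Yes is to be described and taken to the PI.

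**The concern.** The form is built to catch what has changed since the last visit, and it is the step in 7.1 that leads to a PI decision before testing. It re-asks three of the four Experiment 3 exclusions and adds a fifth topic that 4.2 does not list. It leaves out the exclusion that 4.2 names first for TMS. Nothing in the documents explains the omission, and screening is strict on the point: at Visit 1 an unknown family or personal history is treated like a Yes.

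What is at stake is participant safety rather than the treatment comparison. A first seizure between visits, including one after an earlier TMS session, or a family history learned after screening, would not be asked for by the form meant to stop a session.

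**Working it through.** No figure in the plan depends on this, so the check compares the documents item by item.

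**Step 1. Exclusions against the pre-test form.**

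| Item | Excludes from Experiment 3 in 4.2 | On the Visit 1 limiting-criteria checklist | In the TMS block at Visits 2, 8, 9 |
|---|---|---|---|
| Epilepsy or seizures, personal or family | Yes | Yes | No |
| Migraine | Yes | Yes | Yes |
| Benzodiazepines | Yes | Yes | Yes |
| Magnetic-field contraindications | Yes (with Experiment 1) | Yes | Yes |
| Recent concussion | No | Not named | Yes |

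Three of four exclusions carry over. Seizure history is the one that does not.

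**Step 2. Where seizures are asked about.** Before Visit 2 there are three places: the prescreen questionnaire, the Visit 1 medical history summary and the Visit 1 limiting-criteria checklist. On the Contraindications for Lab Testing form it is 0 of 3 visits.

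**Step 3. Other forms that might pick it up after Visit 1.**
- Magnetic-field form: metal, implants and foreign objects only.
- Contraindications for Intervention (Visits 2 to 7): radiating pain, leg weakness and incontinence only.
- Experiment 3 laboratory checklists: no seizure check.
- Health Status Reassessment (Visits 2 to 9): an open question on any change in health. A Yes is recorded, the coordinator alerted and the adverse event log completed. Seizures are not named.
- Change in Medication Use (Visits 2 to 9): records changes in non-back-pain medication over the past 7 days, with the indication. A new drug for seizures could appear here.
- Reassessment physical exam, completed if indicated: has a neurological row and a statement on whether the participant can continue.

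**Step 4. How long each interval is left to the indirect routes.**
- Visit 1 to Visit 2: at most 7 days.
- Visit 2 to Visit 8: the open question is asked at five visits in between (3 to 7).
- Visit 8 to Visit 9: nominally 28 − 3 = 25 days with no visit in between. The open question at Visit 9 covers the whole interval; the medication question covers 7 of the 25 days.

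**Step 5. Exposure.** 60 participants × 3 lab visits = 180 forms before attrition. Visit 2 has TMS before and after the intervention, so sessions number 60 × (2 + 1 + 1) = 240. These count exposures, not expected events.

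**The case against.** A reader might infer from the missing row that a participant with a new seizure would go unasked and be stimulated. The documents do not support that. No answers would be accurate on the four TMS rows, but not on the open health question asked at the same visit, where a Yes alerts the coordinator and goes to the adverse event log. Nor is that question the only other route, since the Change in Medication Use form is a second one. The reassessment exam form is not limited to any one complaint and ends in a decision on continuing.

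The window is also small. Prior history is asked about three times before Visit 2, and diverting Unknown at Visit 1 reduces the scope for a newly learned family history. A history is largely settled at enrolment, whereas migraine and medication change more readily. Section 7.1 speaks of symptoms of contraindicated conditions and does not promise to repeat every 4.2 item, so this is a misalignment rather than a broken commitment.

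The forms shown are v5.0 and the protocol is v6.0. The sponsor correspondence says the e-CRFs were modified for the supplement and that the study was then almost complete for participants with low back pain. No later TMS form is shown.

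All of this narrows the point. It does not remove it. None of these routes asks about seizures. The exam that 7.1 attaches to the open question is triggered there by fever or unexplained weight loss. A newly learned family history is not a change in the participant's own health, so the open question fits it poorly. No text carries a seizure reported by these routes to the PI consultation before TMS. The study also does not treat the open question as sufficient for concussion, which has its own row.

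**Conclusion.** The point holds in a limited form. In the forms shown, the TMS block of the pre-test check omits the seizure exclusion at all three lab visits, while the other three Experiment 3 exclusions are re-asked. The consequence is confined to new or newly disclosed seizures over a participation of about 8 weeks in up to 60 people. Such events could be reported, but only indirectly and without a stated link to the TMS decision. The interval that leans most on a volunteered answer is Visit 8 to Visit 9.

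The likelihood cannot be sized because the documents give no seizure rate; it is presumably low, while the harm could be serious. The conclusion assumes that the v5.0 TMS block was not altered with v6.0, whose revision log lists only editorial changes and the supplemental research. It has no bearing on the efficacy or mechanistic analyses.

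**What to change.** Reconcile Section 4.2, Section 7.1 and the Contraindications for Lab Testing form. Add one row to the Cortical TMS block at Visits 2, 8 and 9 that mirrors the 4.2 exclusion, worded for the time since the last visit and for newly learned personal or family history. Use the form's existing column for describing a Yes and consulting the PI. What follows a Yes remains for the investigators under 7.1; the row sets no new clinical rule. If seizures are instead meant to be picked up through the Health Status Reassessment, Section 7.1 should say so and state how such a report reaches the PIs before TMS.

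The cost is one row on three existing forms and a few seconds per visit.
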